## Abstract

**Background:**

The rise of the internet and related technologies has significant implications for the treatment of complex health problems, including the combination of depression and alcohol/other drug (AOD) misuse. To date, no research exists to test the real world uptake of internet and computer-delivered treatment programs in clinical practice. This study is important, as it is the first to examine the adoption of the SHADE treatment program, a DVD-based psychological treatment for depression and AOD use comorbidity, by clinicians working in a publicly-funded AOD clinical service. The study protocol that follows describes the methodology of this dissemination trial.

**Methods/design:**

19 clinicians within an AOD service on the Central Coast of New South Wales, Australia, will be recruited to the trial. Consenting clinicians will participate in a baseline focus group discussion designed to explore their experiences and perceived barriers to adopting innovation in their clinical practice. Computer comfort and openness to innovation will also be assessed. Throughout the trial, current, new and wait-list clients will be referred to the research program via the clinical service, which will involve clients completing a baseline and 15-week follow-up clinical assessment with independent research assistants, comprising a range of mental health and AOD measures. Clinicians will also complete session checklists following each clinical session with a client, outlining the extent to which the SHADE computer program was used. Therapeutic alliance will be measured at intake and discharge from both the clinician and client perspectives.

**Discussion:**

This study will provide comprehensive data on the factors associated with the adoption of an innovative, computer-delivered evidence-based treatment program, SHADE, by clinicians working in an AOD service. The results will contribute to the development of a model of dissemination of SHADE, which could be applied to a range of technological innovations.

**Clinical trials registry:**

Australian Clinical Trial Registration Number: ACTRN12611000382976.

## Background

Mounting pressure is exerted on the health system by the increasing prevalence of depression and alcohol/other drug (AOD) misuse. These disorders are ranked 3 and 17 in contribution to the global disease burden, with depression elevated to 1st place and alcohol abuse use to 5^th^ among middle-high income countries such as Australia 
[1]. Efficacious treatments have been tested with success for both depression 
[2] and AOD disorders 
[3], suggesting that this burden can be reduced.

Despite this, the gap between need for and receipt of these treatments is large, particularly for counselling 
[4], which is often preferred over pharmacotherapy 
[5]. For example, in the US, 2.1 million people with a 12-month mental disorder did not use services for mental health problems but perceived they had an unmet need 
[6]. Of these, the highest unmet need was for counselling 
[6]. Comorbidity, or the co-occurrence of two or more disorders, is the rule rather than the exception in clinical practice 
[7], with up to 89% of people with AOD use disorders also experiencing depression 
[8]. The presence of comorbid disorders compounds difficulties in treatment access and provision 
[9].

Mental health and AOD researchers and clinicians must respond to these issues, by developing and evaluating treatment programs that address depression and AOD use disorders, whilst minimising cost and maximising efficient use of clinician time and client outcomes. Available evidence-based treatments provide for single problems (e.g. depression or alcohol misuse) rather than the comorbidity with which clients typically present 
[7]. Treatments are often high intensity, require specialist input and training, and are therefore only accessible to a minority of clients 
[10]. For these reasons, many clinicians are not able, or willing, to implement these interventions in practice.

The increased availability and use of computer/internet-based programs as a supplement to health care is also a potential solution to well-documented treatment accessibility problems 
[11], particularly among people with depression and AOD use comorbidity. Interactive and multimedia options offer the potential for higher levels of engagement than other self-help modalities 
[12]. Computers/the internet offer the opportunity for widespread dissemination of treatments, reaching a large audience in a cost effective and timely manner 
[13]. Experts also suggest that the integration of internet/computer-delivered interventions into practice, will increase adherence to evidence-based treatment protocols, and increase the number of practitioners who can deliver highly specialized psychological treatments 
[14].

Internet/computerized CBT treatment programs have established efficacy for a range of mental disorders and other health conditions 
[15]. Our previous work has reported on the efficacy of computerized psychological treatment for concurrent depression and AOD use disorders [SHADE treatment, 16]. In a recent randomized controlled clinical trial involving 97 participants, SHADE computerized treatment was associated with significantly greater reductions in depression relative to a one-session treatment, and equivalent reductions in depression to a face-to-face treatment combining cognitive behavioural therapy (CBT) and motivation enhancement (ME). There was a significant advantage of computerized SHADE for marijuana use over time, with participants in SHADE reporting twice the reduction in marijuana use as the face-to-face condition and approximately five times the reduction as the one-session treatment at 12 month follow-up 
[16]. Computerized SHADE was also associated with similar reductions in alcohol use over 12 months as the equivalent face-to-face-delivered combination CBT/ME program 
[16].

Whilst it is generally accepted that internet/computer-delivered CBT programs are efficacious, with some indicating equivalent benefits to face-to-face-delivered programs, there is very little real world research that demonstrates the benefits and acceptability of these programs in practice and service settings 
[14]. There is some evidence to suggest that, in the US, only 48% of primary care patients would consider using internet-delivered CBT, compared to 91% for traditional face-to-face therapy 
[14]. However, other evidence suggests that clinicians, including psychologists and CBT practitioners, are more open to using these alternatives as supplements to the care they are able to provide 
[17]. Consequently, the current study was commenced with the aim of exploring clinician and client uptake, accessibility and response to a computerized CBT/ME treatment for depression and AOD use (SHADE treatment) within a publicly-funded Drug and Alcohol Clinician Service in New South Wales, Australia.

## Methods/design

### Study aims

The purpose of this original research is to test the effectiveness of the SHADE computerized treatment program, from both a clinician and client perspective, within the real world clinical setting. It is hypothesised that clients exposed to the SHADE program will report superior reductions in depression and AOD use relative to those who are not exposed, and that this response may be moderated by primary drug of concern (e.g. marijuana vs. other drug use), coercion into treatment and computer comfort. It is also hypothesised that there will be an association between clinician openness to innovation, clinician computer comfort and the use of SHADE in clinical practice.

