#### Clinicians

Clinicians will participate in a baseline focus group discussion designed to elicit their attitudes and concerns about adopting innovation into their clinical practice in general, and the SHADE treatment program in particular. Table
1 displays the structure of this focus group discussion.

**Table 1 T1:** Clinician focus group protocol

	
(1)	What sources do you use to inform your clinical practice (e.g. journals, workshops, clinical guidelines)?
(2)	What influences you in deciding on when to use a particular strategy, technique, or resource during a session with a client? How do handouts, self-help books and other information for clients fit into this process?
(3)	Have you incorporated any technology into your sessions with clients already? How did you do that, and what was the result?
(4)	Are there any advantages to using technology, e.g. SHADE, as an adjunct to your clinical practice? And what might the disadvantages or concerns be? What are the main issues?
(5)	What are some of the supervision and supports you think that you might need to have in place to assist you in using technology in your clinical practice?

Subsequent to completing the focus group discussion, clinicians complete two further self-report measures:

(1) Innovativeness Scale 
[21]: a 20-item measure using a 7-point Likert-type scale assessing the likelihood of an individual to adopt innovative strategies in their work.

(2) Computer Opinion Survey 
[22]: a 26-item measure using a 6-point Likert-type scale, developed as a measure of the trait of computer anxiety rather than the “state” of computer anxiety.

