#### Clients

Following the provision of consent, clients complete the following set of assessment measures at baseline and 12-weeks post-baseline via telephone with a trained research clinician, who is independent of the Central Coast DACS. The following questionnaires take between 30-45 minutes to complete:

(1) Demographics: information includes age, gender, occupational and marital status, children, educational experience, ethnicity and current accommodation arrangements.

(2) Service Utilisation: includes current and previous treatments, including self-reported hospitalisations, attendance at clinics, rehabilitation programmes, contact with community mental health teams, psychologists, psychiatrists, other health professionals, involvement in AOD detoxification and counselling, methadone maintenance, 12-step programmes, use of general practitioners, and use of medication (including compliance).

(3) Opiate Treatment Index 
[24]: a quantity/frequency index to estimate average daily use of 11 drug types (alcohol, marijuana, heroin, other opiates, amphetamines, cocaine, hallucinogens, barbiturates, tranquilisers, inhalants and tobacco) in the month prior to assessment.

(4) Treatment Motivation Questionnaire: is a 26 item self-report measure, examining four components of motivation including internal and external motivation, help seeking and confidence in treatment. A 7-point Likert scale is used to examine the level of motivation.

(5) Depression Anxiety Stress Scale 21-item version 
[25]: a 21-item screening tool to for depression, anxiety and stress in the previous 7 days. A 4-point Likert-type scale is used to determine the extent to which a symptom applied to the person.

(6) Global Assessment of Functioning 
[26]: a clinician-rated assessment of current functioning.

(7) Self-compassion Scale 
[27]: is a 26-item measure using a 5-point Likert-type scale assessing the extent to which a person expresses self-compassion towards themselves in difficult times.

(8) Agnew Relationship Measure – Client Version 
[23]: this client-rated measure of therapeutic alliance is similar in content and structure to the therapist-rated version previously described.

We plan to report the cost of delivering the intervention in real world settings and the cost impacts of the outcomes achieved by calibration of selected instruments used in the study (e.g. Quality of Life Scale, Global Assessment of Functioning) with those achieved in other costing studies.

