### Statistical analyses

#### Clients

For the client sample, primary outcome measures are changes in depression, alcohol and marijuana use between baseline and 12-week follow-up.

Previous research using the SHADE resource among substance users 
[16] has resulted in effect size differences of 0.42 between clients exposed to the SHADE resource versus not on depression, alcohol and marijuana use. Assuming similar effect size differences will apply to the current study, we estimate that a sample size of 72 is required at 15-week assessment to achieve adequate power (power = 0.81) to detect differences of this order using repeated measures analysis of variance with an alpha level of 0.05 (calculated using G*Power, version 3.1.2). Predictors of alcohol use, marijuana use and depression at 15-weeks relevant to the current study (e.g. client rated therapeutic alliance, internal and external motivation and coerced vs non coerced clients, exposure to SHADE) will be modelled using a linear regression analysis. This sample size will also enable us to examine an effect size of 0.15 for a linear multiple regression for these outcome variables, with up to 6 predictors, an alpha level of 0.05 and a power co-efficient of 0.80 (actual sample size required = 98).

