### Clinicians

Given the small sample size of clinicians associated with the DACS, descriptive analyses only will be performed on the clinician measures associated with innovation, computer comfort and reported use of the SHADE resource.

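### Computer comfort is a hypothesised moderator of clients' response to SHADE, but no listed client measure records it; the clinician hypothesis and a costing instrument also need reconciling with the methods

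*Protocol article*

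**What the plan says.** **Client moderation.** Study aims states that the client response to SHADE may differ by three factors: "this response may be moderated by primary drug of concern (e.g. marijuana vs. other drug use), coercion into treatment and computer comfort". The next sentence turns to clinicians and expects that "there will be an association between clinician openness to innovation, clinician computer comfort and the use of SHADE in clinical practice". Clinician computer comfort is thus named separately.

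**Client measures.** Under Assessments, Clients, "clients complete the following set of assessment measures at baseline and 12-weeks post-baseline via telephone". Eight numbered items follow: demographics, service utilisation, Opiate Treatment Index, Treatment Motivation Questionnaire, DASS-21, Global Assessment of Functioning, Self-compassion Scale, and the client version of the Agnew Relationship Measure.

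**Clinician measures.** Under Assessments, Clinicians, after the focus group "clinicians complete two further self-report measures": the Innovativeness Scale and the Computer Opinion Survey. The session checklist records whether SHADE was used.

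**Analyses.** The client regression names, as examples, client-rated alliance, internal and external motivation, coercion and SHADE exposure. It is sized "with up to 6 predictors, an alpha level of 0.05 and a power co-efficient of 0.80", requiring 98 clients. For clinicians, "descriptive analyses only will be performed on the clinician measures associated with innovation, computer comfort and reported use of the SHADE resource", and the reason given is their small number.

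**Costing.** The text just below the client battery plans to calibrate "selected instruments used in the study (e.g. Quality of Life Scale, Global Assessment of Functioning") against other costing studies.

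**The concern.** A moderator can be tested only if it is recorded for the people whose response it is supposed to modify, and only if the model contains its interaction with the exposure. For client computer comfort the article provides neither. The timing matters: the score has to be taken at baseline, before exposure to a computer-delivered programme can change it, so the gap cannot be closed once clients have been enrolled.

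Two lesser mismatches sit beside it. The article states a hypothesis about clinicians and then rules out anything beyond description of the same variables, so a reader of the results will not know what would count as support. And one of the two instruments named for costing is described as part of the study but is not listed among the client measures.

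**Working it through.** **1. Each hypothesised factor against its data and analysis**

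| Item | Measured? | Analysis stated? |
|---|---|---|
| Moderator: primary drug | Yes; the Opiate Treatment Index is "a quantity/frequency index to estimate average daily use of 11 drug types", and one of the three counselling teams is a Marijuana Clinic | No interaction named |
| Moderator: coercion | Yes; a named predictor, and MERIT clients are mandated to attend | Main effect named, no interaction |
| Moderator: client computer comfort | No; none of the eight client items | None named |
| Clinician openness, computer comfort, SHADE use | Yes; Innovativeness Scale, Computer Opinion Survey, session checklist | Descriptive only |
| Costing: Global Assessment of Functioning | Yes; item 6 of the client battery | Calibration planned |
| Costing: Quality of Life Scale | Not listed | Calibration planned |

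Only client computer comfort lacks both a measure and an analysis.

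**2. The protocol's regression sample size**

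Inputs from Statistical analyses, Clients: effect size 0.15 (read as Cohen's f²), 6 predictors, alpha 0.05, power 0.80. For the overall R² test the noncentrality is λ = f² × N, with k and N − k − 1 degrees of freedom.

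- N = 97: λ = 14.55, power 0.798.
- N = 98: λ = 14.70, power 0.804.

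The stated 98 reproduces. It is the size for the overall test of six predictors and says nothing specific about moderation.

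**3. What testing moderation would require**

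An illustrative full model has 11 terms: five listed predictors (internal and external motivation counted separately), baseline outcome, primary drug, computer comfort and three SHADE interactions (5 + 1 + 1 + 1 + 3). The relevant test is of the interaction terms given the rest, with q numerator and N − 12 denominator degrees of freedom. At f² = 0.15 and 80% power:

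- three interactions jointly (q = 3): N = 78; power 0.90 at the projected N = 100;
- one interaction (q = 1): N = 55; power 0.97 at N = 100.

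That f² is the protocol's figure for the whole regression and may be optimistic for an interaction. As an assumed contrast, take 100 clients in a balanced 2 × 2 layout (25 per cell, SD 1). The interaction has standard error √(4/25) = 0.40.

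- Interaction of 0.42 SD: 0.42/0.40 = 1.05; power Φ(1.05 − 1.96) = 0.18.
- Interaction of 0.84 SD: 0.84/0.40 = 2.10; power Φ(2.10 − 1.96) = 0.56.

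Power for moderation therefore runs from poor to high depending on an assumption the document does not settle. That supports an exploratory label, not a claim that the sample is too small.

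**4. What 19 clinicians can show**

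Fisher's z with n = 19 has standard error 1/√16 = 0.25.

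- Observed r = 0.4: z = 0.4236; limits 0.4236 ± 0.49, that is −0.066 and 0.914; back-transformed, −0.07 to 0.72.
- True r for 80% power: tanh((1.96 + 0.84) × 0.25) = about 0.60.

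**The case against.** **The clinician restriction is reasoned.** The article explains it by the small number of clinicians, and the figures above bear that out: only a correlation of about 0.6 would be reliably detected. This stands as a reason not to run a confirmatory test. It does not reconcile a stated hypothesis with a descriptive-only plan; an estimate with its interval, labelled exploratory, would.

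**Detail may sit elsewhere.** The predictor list is given as examples, the aim says only that response may be moderated, and interaction terms are often left to an analysis plan. This stands in part: the absence of interaction terms alone would not be a finding. It does not supply a client computer-comfort score, because the client battery is set out item by item and contains none.

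**The moderator might be the clinician's comfort.** The first sentence does not use the word client, and clinician scores could be linked to clients. This is possible, but the sentence concerns client response and the next one specifies the clinician's comfort separately, so the client reading is the more natural.

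**Stronger readings a reader might infer.**
- That all three items lack any measure or analysis. The documents do not support this. The clinician hypothesis has all its measures and a descriptive analysis. Costing keeps the Global Assessment of Functioning and Service Utilisation data, and is a reporting plan, not one of the stated aims.
- That none of the moderation hypotheses can be addressed. Primary drug and coercion both have data.
- That 100 clients are too few because 11 predictors need N = 123. That figure is for the overall R² test. At the same f² the interactions need 78 jointly or 55 singly.

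**Conclusion.** The point holds in a limited form. The main finding is that client computer comfort is a hypothesised moderator with no listed client measure, so it cannot be tested as the article stands. This rests on reading the phrase as the client's own comfort and on taking the eight-item battery as complete.

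The clinician mismatch is secondary: the variables are collected, and what is missing is an analysis that matches the hypothesis. Its size is set by n = 19, the stated maximum, and by treating the association as a correlation between clinician-level scores; any estimate will be imprecise.

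The Quality of Life Scale is a minor inconsistency in the instrument list.

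None of this touches the primary comparison of clients exposed and not exposed to SHADE. The change should be made, and the computer-comfort part first, because it is the hypothesis that fails outright if the baseline score is not collected.

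**What to change.** 1. **Client computer comfort.** Add a short computer-comfort measure to the client baseline interview, or remove computer comfort from the moderation hypothesis. Cost: a few minutes on a 30 to 45 minute interview, or a wording change. If the clinician's comfort was meant, say so and state how it is linked to clients.
2. **Retained moderators.** State that each is tested by a SHADE-by-moderator interaction with its main effects in the model, reported with a 95% interval and labelled exploratory. Cost: a sentence and the extra model terms; intervals may be wide.
3. **Clinician association.** Reword the hypothesis as exploratory and replace the descriptive-only restriction with an estimate and 95% interval. This could be a rank correlation of each clinician score with SHADE use, or a session-level mixed logistic model of SHADE use with a random clinician intercept. Cost: one further analysis, with an interval that will be wide at 19 clinicians and should be shown as such.
4. **Costing.** Add the Quality of Life Scale to the baseline and follow-up battery, or delete the reference and base costing on the Global Assessment of Functioning and Service Utilisation data. Cost: some interview time, or a wording change.

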### Study setting

This is a real world dissemination trial, conducted within a publicly-funded Drug and Alcohol Clinical Service (DACS) on the Central Coast of New South Wales, Australia. It forms part of the area’s general health service for a population of 306,257. The DACS forms part of a general health service, and provides a range of clinical interventions to residents within the catchment area with AOD use problems. Services include counselling, detoxification (hospital-based and outreach), needle and syringe programs, pharmacotherapy services, a diversion program for people with AOD use problems and legal issues (Magistrates Early Referral Into Treatment, MERIT), and a specialist service targeting clients with a primary drug of concern of marijuana. A central intake service acts as the point of initial contact for access to DACS, with subsequent referrals made to relevant services as appropriate. Client and Clinician participants will be recruited from the counselling services associated with the Central Coast DACS. There are three counselling teams within this service, AOD Counselling, Marijuana Clinic and MERIT. In a study conducted at the NSW Central Coast Cannabis Clinic, it was found that clients on average only attended 2.8 treatment sessions, which is lower than the Drug and Alcohol Counselling Team within the same service which had an average of 4.5 treatment sessions in 2006 
[18]. Clients attending the MERIT program are mandated to attend 12 sessions of treatment.

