### Study design

This study is designed to observe, and not prescribe, the use of the SHADE computerized treatment program within the Central Coast DACS. Ethics approval for the study has been obtained from several relevant Human Research Ethics Committees, led by the Northern Sydney Central Coast Human Research Ethics Committee (08/HARBR/78/79), and including the University of Newcastle Human Research Ethics Committee (H-2008-0271), and the Macquarie University Ethics Review Committee (Human Research, 0806-125M(R)).

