#### Clinicians

At information sessions conducted by the authors, clinicians in each team associated with the DACS were introduced to the study and asked to provide consent to participate. Participation involves five activities:

(1) Completion of a baseline focus group discussion regarding the use of innovation in clinical practice.

(2) Completion of a baseline questionnaire regarding their openness to innovation and computer comfort.

(3) Use of the SHADE treatment program with new and ongoing clients in whatever manner they choose, with delivery of the DVD content of the program either contained within the clinic session or provided to clients to complete in their own home in between clinic sessions.

(4) Referral of contact details for new and ongoing clients to the client-data-collection phase throughout the study period, regardless of their exposure to the SHADE treatment program.

(5) Completion of session checklists (see Appendix A) following every counselling session with new and ongoing clients, regardless of their exposure to the SHADE treatment program, and therapeutic alliance measures at intake and discharge for all clients.

Clinicians are provided with a half-day tutorial on the SHADE resource conducted by the research team. The content of this tutorial includes a discussion of the results of the previous clinical trials conducted using the SHADE program, and orientation to the SHADE resource. Clinicians split into groups of two and worked through a different SHADE module on laptops provided by the research team. At the conclusion of this session, clinicians presented each module to the group, and discussed ways in which they felt the module could be integrated into their clinical work at the DACS. Researchers provided their own input into this session where relevant. There was no prescription provided to clinicians as to how, when or with whom the SHADE resource should be used with their clients. However, clinicians suggested that they would use it in the following ways:

(a) “Prescribe” modules for homework in between in-person sessions;

(b) Complete individual modules during the session, sitting side-by-side with clients;

(c) Provide the SHADE resource on DVD-Rom to clients on the wait-list for the DACS;

(d) Use the handouts and worksheets from SHADE to augment discussions about cognitive behavioural skills conducted between clients and clinicians during sessions;

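### The exposed-versus-unexposed SHADE contrast is likely to be confounded by the amount of counselling received, and no stated analysis accounts for sessions attended

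*Protocol article*

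**What the plan says.** All references are to the protocol article.

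- **Design.** Under Study design: "This study is designed to observe, and not prescribe, the use of the SHADE computerized treatment program within the Central Coast DACS". The Clinicians subsection adds: "There was no prescription provided to clinicians as to how, when or with whom the SHADE resource should be used with their clients".
- **Delivery.** The same subsection describes the DVD content as "either contained within the clinic session or provided to clients to complete in their own home in between clinic sessions". Of the five uses that clinicians suggested, four (homework modules, side-by-side use, handouts, video in the group program) run through sessions or groups. The fifth does not: "Provide the SHADE resource on DVD-Rom to clients on the wait-list for the DACS".
- **Attendance.** Study setting reports that in the Cannabis Clinic "clients on average only attended 2.8 treatment sessions", that the Drug and Alcohol Counselling Team "had an average of 4.5 treatment sessions in 2006", and that "Clients attending the MERIT program are mandated to attend 12 sessions of treatment". The clinician part of Sample size calculation uses a service-wide average of three.
- **Contrast and analysis.** Study aims hypothesises larger reductions in depression and AOD use among exposed clients than among unexposed clients. Statistical analyses (Clients) plans a repeated measures ANOVA and names no covariate. A linear regression follows, whose example predictors are client-rated alliance and "internal and external motivation and coerced vs non coerced clients, exposure to SHADE".

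**The concern.** If SHADE can be introduced at any session, each further session is another chance to become exposed. A client who leaves after one or two visits then tends to be counted as unexposed. That client can still contribute an outcome, because follow-up is by telephone with research staff independent of the service. The two groups would then differ in how much ordinary counselling they received as well as in SHADE.

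The Background gives reason to think that dose matters. In the earlier trial SHADE cut marijuana use by twice as much as face-to-face treatment and about five times as much as a single session. Face-to-face treatment therefore achieved roughly 5 / 2 = 2.5 times the single-session reduction, although the article reports no test of that pair. A contrast between clients who stay and clients who leave early resembles that comparison and could show a difference even if SHADE added nothing. At stake is whether the effectiveness hypothesis in Study aims can be read from this contrast.

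**Working it through.** **Plan's own figures.** The article gives no figure for counselling dose by exposure, so there is none to reproduce on this point. Its sample sizes serve below only as yardsticks. The regression figure of 98 reproduces (effect size 0.15, six predictors: power 0.8035 at 98 and 0.798 at 97). The 72 depends on inputs that are not stated, and nothing here rests on it.

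**Inputs from the article.** Mean sessions m: 2.8 (Marijuana Clinic), 4.5 (AOD Counselling), 3 (service-wide); 100 clients retained.

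**Assumptions.** Attendance is geometric with mean m, so the chance of leaving after any session is q = 1/m. The chance p of first receiving SHADE is the same at each session. SHADE does not change attendance.

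**Formulas.** Let c = 1 − (1 − q)(1 − p).
- Proportion never exposed: U = q(1 − p)/c
- Mean sessions, unexposed: 1/c
- Mean sessions, exposed: (m − U/c)/(1 − U)

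**Worked case, m = 3, p = 0.2.** q = 0.333 and c = 1 − 0.667 × 0.8 = 0.467. U = 0.333 × 0.8 / 0.467 = 0.571. Unexposed mean = 1/0.467 = 2.14. Exposed mean = (3 − 0.571 × 2.14)/0.429 = 4.14.

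| Setting (p = 0.2) | Ever exposed | Exposed mean | Unexposed mean |
|---|---|---|---|
| Marijuana Clinic, m = 2.8 | 41% | 3.9 | 2.1 |
| AOD Counselling, m = 4.5 | 53% | 6.1 | 2.6 |
| Service-wide, m = 3 | 43% | 4.1 | 2.1 |

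**Sensitivity to p.** At m = 3 the means are 4.5 v 2.5 for p = 0.1 and 3.9 v 1.9 for p = 0.3. Under geometric attendance the gap is always m − 1 (here two sessions), whatever p is, because a client's expected further sessions after first exposure are m − 1.

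**Sensitivity to the shape of attendance.** With less variable (shifted Poisson) attendance and no MERIT clients, exposed and unexposed clients average about 4.4 to 4.6 v 3.1 to 3.7 sessions for p from 0.05 to 0.2. The gap is smaller but has the same sign.

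**Sensitivity to wait-list DVDs.** This uses shifted Poisson attendance, an assumed team mix of 30% Marijuana Clinic, 50% AOD Counselling and 20% MERIT, and wait-list clients with no sessions. The exposed group still had more sessions in every case tried except one. With 30% of clients on the wait-list, 90% of those given the DVD and p = 0.1, the means were 3.7 exposed and 4.0 unexposed.

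**What this could do to the outcome.** At m = 3 the SD of geometric sessions is √(1 − q)/q = √0.667/0.333 = 2.45, so the gap is 2/2.45 = 0.82 SD of sessions. If sessions and outcome correlate at r, and linearly, a SHADE effect of zero would appear as about 0.82r outcome SDs: 0.08 at r = 0.1, 0.24 at r = 0.3 and 0.41 at r = 0.5. The article gives no value of r. The last figure is close to the planned 0.42, if that is read as a standardised mean difference.

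**The case against.** The strongest reply is that much of this is inference. No section defines when exposure is counted, states that it depends on session count, or reports that exposed clients receive more counselling. Those details may sit in an analysis plan that is not shown. The predictor list is given by way of example, so sessions are not ruled out. Coercion is a named predictor and a stated moderator, and plausibly captures part of the MERIT difference. The wait-list route needs no session at all. Current clients enter part-way through treatment, so whole-episode averages need not describe the follow-up window.

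These points stand as limits on certainty and size. They do not remove the concern. The contrast and its test are stated, and the ANOVA names no adjustment. Coercion does not address differences in attendance within the voluntary teams.

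Two stronger readings are tempting. A reader might infer that the bias certainly favours SHADE; the wait-list route prevents that. A reader might also pool the three teams equally with MERIT fixed at 12 sessions, which at p = 0.2 gives 8.6 v 2.9. That mix implies a mean of (2.8 + 4.5 + 12)/3 = 6.4 sessions, against the service average of three, and the article supports neither the equal mix nor full attendance of the mandated sessions.

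**Conclusion.** The concern holds as a likely, unaddressed confounder of the main client contrast. Under the stated assumptions exposed clients would receive roughly twice the counselling of unexposed clients: a gap of about two sessions at the service mean of three, 1.8 in the Marijuana Clinic and 3.5 in AOD Counselling. The gap is smaller if attendance is less variable than geometric or if SHADE is mostly introduced early. The probable direction favours SHADE. The size of any bias in the outcomes depends on the unknown correlation between sessions and outcome, so no single figure for it is claimed. As planned, the contrast supports an association between SHADE exposure and outcome, but not a separate effect of SHADE.

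**What to change.** 1. Keep the planned analysis on all retained clients, but adjust the exposure contrast for counselling team (AOD Counselling, Marijuana Clinic, MERIT). Report clients who were only ever on the wait-list separately.
2. Prespecify two supportive analyses. The first is a landmark analysis: exposure means SHADE used or issued by a set early session, among clients who attended at least that many, with later first use counted as unexposed. The second is the planned regression with sessions attended added. Read the second with caution, because total sessions may follow from exposure, and adjusting for them could then remove or distort a real effect.
3. State the Study aims result as an association, and do not claim effectiveness unless it is consistent across these analyses.

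**Cost.** The changes are mainly analysis wording, with three consequences.
- A landmark at the second session drops single-session clients. Under geometric attendance that is 1/m: 36% at 2.8, 22% at 4.5 and 33% at 3. At the service mean about 67 of 100 remain, below both 72 and 98, which is why it can only be supportive. Late first use also dilutes its contrast.
- Client-level attendance data are needed. Checklists will not do, since only 50% completion is expected. The article cites service data on occasions of service only as an average, so access to individual records must be confirmed.
- Team takes two regression terms. With the five named predictors (alliance, internal motivation, external motivation, coercion, exposure) that makes seven, and sessions makes eight, against the six that were sized. At effect size 0.15 and power 0.80 the required numbers become 103 and 109, against 100 projected. Coercion and MERIT membership may overlap, so check whether both terms are needed.
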